# Prophylactic prednisolone for the prevention of early and intermediate adverse effects of radioactive iodine therapy in patients with thyroid cancer: study protocol for a single-centre, phase II/III, randomized, double-blinded, placebo-controlled clinical trial

**DOI:** 10.1186/s13063-020-04744-x

**Published:** 2020-09-29

**Keywords:** Prednisolone, Adverse effects, Radioactive iodine therapy, Thyroid cancer, Study protocol, Randomized control trial

## Abstract

**Background:**

Radioactive iodine (RAI) therapy is the standard adjuvant treatment for differentiated thyroid cancer (i.e. papillary and follicular). RAI is associated with troublesome early, intermediate and late adverse effects. Although glucocorticoids are used for the management of these adverse effects, there is little evidence regarding the effectiveness of prophylactic glucocorticoids to prevent these complications. This trial will evaluate the efficacy of a short course of prophylactic glucocorticoids in the prevention of adverse effects of RAI treatment in patients with differentiated thyroid cancer.

**Methods:**

A phase II/III, single-centre, randomized, double-blinded, placebo-controlled, parallel-arm clinical trial will be conducted. Patients with differentiated thyroid cancer who are referred to RAI therapy at the National Cancer Institute, Sri Lanka, will be randomized into two arms consisting of 200 patients each. The experimental group will receive prophylactic oral prednisolone 0.5 mg/kg and omeprazole 20 mg single dose 6 h before RAI therapy followed by oral prednisolone 0.5 mg/kg and omeprazole 20 mg daily for 3 days. The control group will receive oral placebo and omeprazole 20 mg single dose 6 h before RAI therapy followed by oral placebo and omeprazole 20 mg daily for 3 days. Clinically significant adverse effects assessed as related to RAI as well as prednisolone therapy and the quality of life parameters will be compared between the two groups.

**Discussion:**

If proven beneficial, this intervention can be incorporated into the standard practice to reduce early and intermediate adverse effects of RAI for thyroid cancer with a potential improvement of quality of life.

**Trial registration:**

Sri Lanka Clinical Trials Registry SLCTR/2020/009. Registered prospectively on 23 February 2020. Items of the WHO Trial Registration Data Set are provided in the supplementary file.

## Background

Radioactive iodine (RAI) ablation following thyroidectomy is the standard of care for most patients who are diagnosed with differentiated thyroid carcinoma [1–3]. RAI is administered with the primary objective of eliminating any residual thyroid cancer cells. The secondary objectives of RAI include improving the sensitivity of serum thyroglobulin assays during follow-up and improving the sensitivity of detection of both local and/or metastatic disease through functional and cross-sectional imaging [2, 4].

RAI is usually well-tolerated but is known to be associated with several adverse effects. Early adverse effects (up to 10 days after treatment) include local side effects (transient neck pain and swelling), salivary related (acute sialadenitis and xerostomia), nasal related (abnormalities in smell, epistaxis) and gastrointestinal side effects (ageusia, nausea, vomiting, stomatitis and ulcers). The incidence of early adverse effects is reported to be 10–20% for radiation thyroiditis and tumour swelling and 12–67% for acute radiation sialadenitis [5, 6]. Intermediate (10 days to 3 months) and late (after 3 months of treatment) adverse effects commonly include salivary-related side effects (recurrent chronic sialadenitis, xerostomia, salivary duct obstruction), eye-related adverse effects (xerophthalmia, epiphoria, conjunctivitis, nasolacrimal outflow obstruction) and dysfunction of body organs including pulmonary, gastrointestinal, haematopoietic systems and gonads [2, 4, 7, 8]. Chronic sialadenitis, xerostomia and abnormalities in taste or smell have been reported in approximately 20% and usually seen after multiple therapy. Other long-term adverse effects such as other organ involvement (pulmonary fibrosis, bone marrow suppression, etc.) are rare and seen in less than 1% [2, 6]. Furthermore, more serious late adverse effects such as second primary malignancies have also been reported, which however are rare. Although most of these complications are rarely serious or life threatening, they can have a significant impact on patients’ quality of life [4]. Radioactive iodine therapy is generally administered with high doses of a radioactive isotope of iodine (iodine-131), and in certain occasions, several cycles of treatment may be needed for an adequate response, particularly in cases of recurrent diseases or progressive iodine-avid metastatic diseases. Such instances substantially increase the possibility of adverse effects of RAI [4].

In a single-blind randomized study, Silberstein et al. assessed the efficacy of pilocarpine in the prevention of radiation sialadenitis and other adverse effects of RAI [9]. In this study, prophylactic glucocorticoids were given for a period of 3 days in both treatment and placebo arms. All patients received a combination of 8 mg of dexamethasone and 100 mg of dolasetron mesylate orally 2 h before therapy and every 12 hourly for another 5 doses after RAI ingestion in addition to the sialorrheic therapy with or without pilocarpine, 5 mg 8-hourly orally for 1 week [9]. Although pilocarpine was not associated with reduction in the adverse effects of RAI, the overall incidence of the adverse effects was considerably lower compared to previous data with only 5% acute and 1.66% chronic sialadenitis. This probably was due to the prophylactic glucocorticoids used in this study. However, no randomized study to date has studied the effects of steroids on the prevention of complications of RAI.

### Study rationale

Although glucocorticoids have been indicated in the management of certain adverse effects (early and intermediate), there is no clear evidence on its effectiveness in the prevention of adverse effects in the context of routine RAI treatment of thyroid cancer. Furthermore, due to the lack of robust evidence, the usage of glucocorticoids in the management varies depending on the individual perceptions and clinical experiences. Short-term glucocorticoid prophylaxis is inexpensive, is economically feasible and is well tolerated with minimal side effects. Thus, this study is aimed to assess the usefulness of glucocorticoids versus placebo for the prevention of early and intermediate adverse effects and the impact on quality of life following RAI treatment in thyroid cancer patients.

### Study objectives

#### Primary objectives

To estimate the impact of glucocorticoids on the incidence of predefined clinically significant early and intermediate adverse effects of RAI between patients treated with prophylactic prednisolone versus controls over a period of 3 months after completion of RAI.

#### Secondary objectives

To estimate the impact of glucocorticoids on the incidence of early and intermediate adverse effects of RAI during the first 3 months post therapy (all types, all grades, any duration).To describe comparatively between treatment and control groups the onset, duration, recurrence and severity of early and intermediate adverse effects of RAI during the first 3 months after completion of RAITo evaluate the impact of glucocorticoids on the incidence, severity and type of all adverse effects assessed as related to glucocorticoidsTo evaluate the impact of glucocorticoids on the patient-reported outcomes related to adverse effects of RAI at 2 weeks and 3 months after completion of RAITo study the impact on the quality of life at 2 weeks and 3 months, first overall between treatment groups, then focusing on patients who have experienced a complication of RAI

## Methods

### Study design

A phase II/III, single-centre, randomized, double-blinded, placebo-controlled, parallel-arm clinical trial with a superiority framework comparing prophylactic glucocorticoids versus a placebo will be performed with a minimum of 200 patients allocated to each arm.

### Study population

Adult patients with well-differentiated (i.e. papillary and follicular) thyroid cancer who are referred to RAI therapy at the National Cancer Institute, Sri Lanka.

### Subject eligibility

Patients will be included in the trial only if they meet all of the following inclusion criteria and none of the exclusion criteria. No exceptions, waivers or exemptions will be granted.

### Inclusion criteria

Patients with histologically proven differentiated thyroid cancer following total thyroidectomy and are eligible for RAI therapy, referred to the National Cancer Institute, Sri Lanka, will be invited to participate in this study.No prior history of radiotherapyAge > 18 yearsAn Eastern Cooperative Oncology Group (ECOG) performance status score of 0–1Patients must have normal marrow function as defined below:
Leukocytes > 3000/μLAbsolute neutrophil count > 1500/μLPlatelets > 100,000/μLIn females of the reproductive age group, exclusion of pregnancy before commencing RAI and avoiding future pregnancy for 6 months using contraceptives will be mandatory. Therefore, such patients who are capable of childbearing on adequate contraception will be included in this study.Available for follow-up and management in the study centre for at least 6 monthsInformed, voluntary, written consentPatients must sufficiently understand to fill in the quality of life and patient-reported outcome measures questionnaires.

### Exclusion criteria

Those with absolute and relative contraindications for glucocorticoids such as uncontrolled diabetes mellitus, gastric and duodenal ulcers, immunosuppression, ongoing or active infections and chronic infective diseasesHistory of previous RAI therapyPrevious major head and neck surgeryPatients with previous history of salivary gland diseases, such as sialadenitis, duct obstruction and calculi, and ophthalmological diseases such as xerophthalmia and conjunctivitisUncontrolled concurrent illness including, but not limited to, symptomatic congestive heart failure, unstable angina pectoris, cardiac arrhythmia or psychiatric illness/social situations (within 12 months before the study) that would limit compliance with study requirements.Pregnant women and breast-feeding mothers are excluded as RAI therapy is contraindicated in such patientsDiagnosed HIV-positive patients on combination antiretroviral therapy are ineligible as glucocorticoids may further suppress the immunity and increase the chances of opportunistic infectionPrior diagnosis of cancer that was:
More than 5 years prior to current diagnosis with subsequent evidence of disease recurrence or clinical expectation of recurrence is greater than 10%Within 5 years of current diagnosis with the exception of successfully treated basal cell or squamous cell skin carcinoma or carcinoma in situ of the cervix

### Recruitment strategies

All eligible patients referred to the National Cancer Institute, Sri Lanka, will be identified prospectively from the outpatient clinics during the first visit and will be invited to participate in the study. After obtaining informed written consent, they will be randomized to either intervention or placebo arm based on a computer-based random number generator. Randomization will be stratified by the total dose of radioactive iodine into 50–100, > 100 and < 200, and > 200 mCi. Recruitment will be allocated to each group in a ratio of 1:1:1. Patients will be recruited until a maximum number of 70 is achieved in each of the 3 arms. Patients who withdraw their consent to participate prior to response evaluation will be replaced.

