#### Randomization (or stratification) procedures

At study entry, patients will be randomly allocated to one of the two arms, the intervention arm and the placebo arm. Randomization will be balanced (1:1), using permuted blocks, and stratified according to the total dose of RAI given for stratification into three groups. Criteria for stratification will be 50–100, > 100 and < 200, and > 200 mCi.An independent investigator will be responsible for randomization of treatment using an online randomization software, ensuring concealment of treatment allocation for the next patient.

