### Data analysis

#### Sample size calculation

The reported rates of radiation thyroiditis are approximately 20% whilst acute radiation sialadenitis is 12–67% and chronic sialadenitis and xerostomia were 20% [5, 6]. Based on these available data, we assume that clinically significant adverse effects will be reported at 3 months in 20% of patients. At a 2-sided 5% alpha level, a total of 200 patients in each group is required to ensure an 80% power if glucocorticoids are associated with a 10% absolute reduction (10% vs. 20%).

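### The recruitment stopping rule (70 in each of three arms, 1:1:1) contradicts the two-arm, 1:1 design with at least 200 per arm; on one reading it stops the trial at 210 patients with about 53% power

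*Protocol article*

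**What the plan says.** All references are to the protocol article.

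- **Recruitment strategies** first sends patients to either the intervention or the placebo arm and names three RAI dose strata. It then says: "Recruitment will be allocated to each group in a ratio of 1:1:1", and next: "Patients will be recruited until a maximum number of 70 is achieved in each of the 3 arms".
- **Study design** describes a parallel-arm, placebo-controlled trial "with a minimum of 200 patients allocated to each arm". The Abstract likewise gives two arms of 200.
- **Study assessments** says that patients in each dose group are randomised to two arms, experimental and placebo.
- **Randomization (or stratification) procedures** says: "Randomization will be balanced (1:1), using permuted blocks", stratified by the three dose groups.
- **Sample size calculation** assumes a 20% event rate at 3 months, falling to 10% with glucocorticoids, and states: "At a 2-sided 5% alpha level, a total of 200 patients in each group is required to ensure an 80% power".

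**The concern.** The sentence in Recruitment strategies is the only one in the article that says when enrolment stops, and it does not fit the rest of the design. It names three arms where there are two, gives a three-way ratio where allocation is 1:1, and sets a maximum which, added up as written, is 210 patients. Study design sets a minimum of 400. A maximum of 210 and a minimum of 400 cannot both be met.

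What is at stake is the primary comparison. If the cap were applied as a total per dose stratum, the trial would close 190 patients short of 400 (47.5%). It would then have little better than an even chance of detecting the effect it was sized for.

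**Working it through.** **Inputs, all from Sample size calculation:** p1 = 0.20 (control), p2 = 0.10 (prednisolone), two-sided alpha 0.05 (z = 1.960), power 80% (z = 0.8416), equal allocation. No inflation for dropout is stated. The cap of 70 and the count of three come from Recruitment strategies.

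**Step 1: reproduce the plan's own figure.** Pooled-variance formula for two proportions, with mean proportion 0.15:

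n per arm = [1.960 × √(2 × 0.15 × 0.85) + 0.8416 × √(0.20 × 0.80 + 0.10 × 0.90)]² / 0.10²

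= [1.960 × 0.5050 + 0.8416 × 0.5000]² / 0.01 = (0.9897 + 0.4208)² / 0.01 ≈ 199

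The stated 200 per group is confirmed. Other uncorrected formulas give 195 to 197. A continuity correction gives 219, so the plan evidently used none.

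**Step 2: what the cap could mean.**

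| Reading of 70 in each of three arms | Total | Per treatment arm |
|---|---|---|
| 70 per dose stratum, both treatments together | 3 × 70 = 210 | 105 |
| 70 per dose stratum within each treatment arm | 3 × 70 × 2 = 420 | 210 |
| Three treatment arms of 70 | 210 | 70 |

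**Step 3: power on each reading.** Power = Φ[(0.10 × √n − 0.9897) / 0.5000]:

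- n = 200 (plan): (1.4142 − 0.9897) / 0.5 = 0.849, power 80.2%
- n = 105: (1.0247 − 0.9897) / 0.5 = 0.070, power 52.8%
- n = 210: (1.4491 − 0.9897) / 0.5 = 0.919, power 82.1%
- n = 70: (0.8367 − 0.9897) / 0.5 = −0.306, power 38.0%

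The choice of uncorrected method hardly matters. At 105 per arm the unpooled formula gives 53.6%, the arcsine formula 53.8%, and exact enumeration of the uncorrected chi-square test 53.8%.

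**Step 4: precision.** The half-width of the 95% confidence interval for the risk difference is 1.96 × √[(0.16 + 0.09) / n]. That is 6.9 percentage points at 200 per arm and 9.6 at 105. With 105 per arm, 80% power would need a fall from 20% to about 6.9%, not to 10%.

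**The case against.** The strongest reply is that 70 was meant per dose stratum within each treatment arm. The numbers suit this: 200 / 3 = 66.7, which rounds up naturally to 70, and 3 × 70 = 210 sits just above the stated minimum of 200 per arm. Study assessments describes exactly this three-by-two layout. On this reading no power is lost. The reply is a good one, and it rules out presenting 53% as the plain consequence of the plan. It remains an inference, though. The sentence caps three units, calls them arms, and contains no factor of two. Simply changing arms to strata gives 210 patients, not 420. Even on the favourable reading, the number of arms and the 1:1:1 ratio are misstated.

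A second reply is that the planned size is not in doubt. Three sections give 200 per arm, and this is a single-centre trial enrolling under the direct supervision of senior investigators. That makes an accidental stop at 210 less likely but does not exclude it.

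A reader might also infer more than the article supports:

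- *That there is a third treatment arm, with 38% power for a pairwise comparison.* Nothing else in the article describes one.
- *That equal stratum quotas would stall recruitment on the rarest dose group, or make the overall event rate unrepresentative of referred patients.* Both depend on the referral mix by dose. Feasibility gives only about 500 referrals a year, with no breakdown. Equal quotas are a design choice, and the analysis is adjusted for the stratification factors.

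**Conclusion.** The stopping rule is wrong as written: it contradicts the number of arms, the allocation ratio and the minimum sample size given elsewhere in the same article. The sample size calculation itself is sound.

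The consequence is conditional. If 70 is the total for each dose stratum, the trial ends at 105 per arm with about 53% power. If it is 70 per stratum per treatment arm, the trial ends at 210 per arm with about 82% power, and the defect is confined to the wording. The article does not settle which was intended, so it does not support a flat statement that the trial is underpowered.

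These figures assume the plan's own 20% and 10% event rates, a simple two-proportion comparison without continuity correction, an even split between treatments, every stratum filling to its cap, and no loss to follow-up.

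**What to change.** Replace the two sentences carrying the 1:1:1 ratio and the cap of 70 with, for example: *Patients are randomised 1:1 to the two treatment arms within each RAI dose stratum, and recruitment continues until at least 200 patients per arm (400 in total) are randomised.* If stratum caps are intended they can stay, provided they are given per stratum per treatment arm and add up to at least 200 per arm.

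The cost is a short text amendment. Under Protocol waiver/deviations/violation it needs ethics committee approval before it takes effect. Trial status says recruitment has not begun, so no enrolled patient is affected, and the planned 400 does not change.

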### Study assessments

Participants will be given an information sheet and will be explained in detail about the study, and informed written consent will be taken prior to recruitment. The basic demographic information including age, sex, ethnicity and medical history including the details related to thyroid cancer (such as type, grade, stage, lymph node involvement), comorbidities and the current treatment will be collected using the clinic notes and interviewer-administered questionnaire. The contact details will also be collected for the purpose of follow-up. A general physical examination will be performed for a baseline assessment prior to administration of RAI. Basic haematological parameters including full blood count and renal functions will be performed before RAI treatment. A baseline quality of life scores which are EQ-5D-5L and FACT H&N will be measured [10]. Data collection tool is attached in the Supplementary file.

Patients will be stratified based on the dose of the RAI into three strata (50–100, > 100 and < 200, and > 200 mCi) based on the American Thyroid Association Guidelines 2015 [11]. From each group, patients will be randomized to two arms, the experimental and the placebo arms. All patients will be given a diary and asked to keep a log of any new symptoms after RAI therapy. Patients in both groups will be instructed to have sugar-free hard candy or gum in their mouths at all times when awake for a period of 1 week. Proton pump inhibitors are routine given in our setting to minimize dyspeptic symptoms which are reported to occur in around 50% and thus will be given to both arms [5]. This will also be helpful to minimize the gastrointestinal adverse effects of glucocorticoids. At least a fluid input of 2400 mL will be maintained during the first week after therapy. If a patient develops adverse effects of RAI, symptomatic management would be given, and the given treatment will be documented. Each patient will be reviewed at 2 weeks and 3 months by history, examination to assess for abovementioned side effects, for the measurement of quality of life scales and for possible complications of glucocorticoids. The onset, duration, recurrence and rate of each early and intermediate adverse effect will be assessed by a clinical interview and examination. For the grading of severity of the adverse effects, the Common Terminology Criteria for Adverse Effects version 4.0 will be used for an objective assessment by the clinician. Furthermore, the Patient-Reported Outcome version of the Common Terminology Criteria for Adverse Effects questionnaire will also be used to get the patient’s perspective regarding the presence of symptoms and their severity. After the study has been completed, patients will be subjected to standard routine follow-up for thyroid cancer.

### Study treatment and dosing schedule (dose, frequency and duration of the experimental treatment)

The treatment group includes oral prednisolone 0.5 mg/kg (maximum 40 mg) with omeprazole 20 mg single dose 6 h before RAI therapy and followed by daily (mane) with meals for 3 days. The control group includes oral placebo and omeprazole 20 mg single dose 6 h before RAI therapy and followed by daily (mane) with meals for 3 days. A placebo was chosen as the comparator as currently there is no alternative drug proven to reduce the adverse effects of RAI. If a dose is missed, the missed dose should be taken at the time of identification of the missed dose if it is during the same day and the next dose should be taken at the scheduled time.

The investigational drug formulation will be manufactured following all regulations. The placebo will be starch tablets of similar external features. The drug and the placebo will be specifically manufactured by the State Pharmaceutical Corporation of Sri Lanka for this study, and therefore, the quality of drug will be ensured.

The study investigators are responsible for enrolling participants, and this will be under the direct supervision of the principle investigator and the senior investigator. Blinding will be ensured by making sure that only one independent investigator will assign the drug and the placebo as either A or B randomly by computer-generated numbers and will be allocated to the next investigator as either drug A or drug B using sealed envelopes, who will be in charge of the drug administration. The details of identification of A and B will be concealed under lock and key until the data collection is complete to the other investigators. Thus, both the investigator and patient will be blinded. Unblinding will be permissible in the event of a severe adverse (CTCAE grade 4) event either due to RAI or prednisolone. In such instances, the investigators and clinicians taking care of the patients will decide on unblinding.

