### Endpoint definitions

#### Primary outcome

Onset of one or more of predefined clinically significant adverse effects assessed as due to RAI during the 3-month period following completion of RAI treatment.

Side effects of RAI treatment will all be assessed clinically as there are no reliable tests to assess the side effects. The majority of the steroid-related side effects will also be assessed clinically, except capillary blood sugar level which will be assessed daily by the patient if on treatment for diabetes mellitus. Those without diabetes mellitus will not undergo routine capillary blood sugar monitoring as short-term, low-dose prednisolone does not warrant routine blood sugar monitoring in healthy individuals, in contrast to long-term administration [12]. The details and definitions of the adverse effects are given in Table 1. Clinically significant adverse effects are defined as the maximum severity of the adverse events assessed as related to RAI reaching the predefined level mentioned in Table 1 and/or if symptoms defined in Table 1 of any level of severity persisting for a prolonged (more than 2 weeks) duration.

**Table 1 Tab1:** Definition of clinically significant outcomes

Related to	Classification	Symptom	Definition	CTCAE grade and definition
RAI	Local	Neck pain	A disorder characterized by marked discomfort sensation in the neck area	Grade 2 (impairment of instrumental activities of daily living) and above
RAI	Local	Neck swelling	A disorder characterized by marked enlargement in the neck area	Grade 2 (impairment of instrumental ADL) and above
RAI	Local	Dysphagia	A disorder characterized by difficulty in swallowing	Grade 2 (symptomatic and altered eating/swallowing) and above
RAI	Local	Dyspnoea	A disorder characterized by difficulty in breathing	Any grade
RAI	Oral	Sialadenitis	A disorder characterized by an inflammatory process involving the salivary gland	Grade 2 (moderate symptoms; oral intervention indicated) and above
RAI	Oral	Dry mouth	A disorder characterized by reduced salivary flow in the oral cavity	Grade 2 (moderate symptoms; oral intake alterations; unstimulated saliva 0.1 to 0.2 mL/min)
RAI	Oral	Oral mucositis	A disorder characterized by inflammation of the oral mucosal	Grade 2 (moderate pain; not interfering with oral intake; modified diet indicated) and above

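### Drug A and drug B share one key for the whole trial, so unblinding one patient discloses the arm of every patient whose letter is known

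*Protocol article*

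**What the plan says.** The blinding method is in the protocol article, in the section on study treatment and dosing schedule. It has four parts.

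- **Labels.** "only one independent investigator will assign the drug and the placebo as either A or B randomly by computer-generated numbers".
- **Who receives the letters.** Each allocation is passed as a letter to the person who gives the treatment: it "will be allocated to the next investigator as either drug A or drug B using sealed envelopes, who will be in charge of the drug".
- **The key.** "The details of identification of A and B will be concealed under lock and key until the data collection is complete to the other investigators".
- **Unblinding.** "Unblinding will be permissible in the event of a severe adverse (CTCAE grade 4) event either due to RAI or prednisolone". In that case "the investigators and clinicians taking care of the patients will decide on unblinding".

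The randomization section adds 1:1 permuted blocks stratified by RAI dose, and online software run by an independent investigator, "ensuring concealment of treatment allocation for the next patient". It mentions no patient-specific code or kit number.

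On the endpoint, the primary outcome section says: "Side effects of RAI treatment will all be assessed clinically as there are no reliable tests to assess the side effects". An event counts only if it is attributed to RAI. The follow-up section has the investigator record the CTCAE grade.

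**The concern.** A two-letter scheme keeps the blind with a single secret. That works only if the secret is never used before the trial ends, and this protocol provides for its use during the trial. Once the meaning of one letter is known, so is the meaning of the other, and the disclosure reaches beyond the patient for whom it was needed.

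What is at stake is the primary endpoint. It has no laboratory or imaging anchor: a clinician grades symptoms and judges whether RAI caused them. Table 1 lists dyspepsia and abdominal pain under both RAI and glucocorticoids, so for those symptoms the attribution is a choice between RAI and the study drug. A grader who knew the arm could shift either judgement without intending to. A code broken part-way through cannot be restored for the patients still to be assessed.

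**Working it through.** **1. What is labelled.** The things assigned to A or B are the drug and the placebo, that is, two products. What is locked away is the identity of A and of B. Read naturally, this is one key for the whole trial, not a list of patient codes.

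**2. What one unblinding discloses.** Suppose patient *i* carries letter A and is unblinded.
- Patient *i*'s treatment plus patient *i*'s letter gives the meaning of A, and therefore of B.
- The meaning of A and B plus patient *j*'s letter gives patient *j*'s arm, for every *j*, already treated or still to come.

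So the disclosure reaches everyone whose letter is known to those who learn the key. The administering investigator is given the letters. The article does not say whether the person who grades outcomes is someone else, or is kept from the letters.

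**3. The two statements on the key, side by side.** The key is to stay "concealed under lock and key until the data collection is complete to the other investigators". Yet unblinding may happen earlier, and investigators are among those who decide on it. With patient-level codes both statements could hold. With a single A/B key they cannot both hold once a code is broken for someone who knows the letter.

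**4. The plan's own figure, as background.** The sample size section gives 200 per arm for 20% vs 10%, two-sided 5%, power 80%. With pooled variance:

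n = [1.960·√(2·0.15·0.85) + 0.842·√(0.20·0.80 + 0.10·0.90)]² / 0.10² = 199 per arm; the power at 200 per arm is 80.2%.

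The stated figure reproduces. The total used below is 2 × 200 = 400.

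**5. Chance of at least one eligible event.** The article gives no grade 4 rate, so the rate *p* is assumed. The chance is 1 − (1 − p)^400.

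| Assumed p per patient | Expected events (400p) | Chance of at least one |
|---|---|---|
| 0.01% | 0.04 | 4% |
| 0.1% | 0.4 | 33% |
| 0.25% | 1.0 | 63% |
| 0.5% | 2.0 | 87% |

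These are chances of an event that would permit unblinding. The chance of an actual code break is lower, by an unknown factor.

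**6. What a break could do to the test (illustration).** Take no true effect, 20% in both arms and 200 per arm. Suppose that knowing the arm lowers recorded events in the prednisolone arm by *b*, in the share *f* of patients assessed after the break. The recorded rate there is 0.20 − f·b. The two-sided rejection rate is

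Φ[(Δ − 1.96·SE₀)/SE₁] + Φ[(−Δ − 1.96·SE₀)/SE₁],

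where Δ = f·b, SE₀ is the pooled and SE₁ the unpooled standard error.

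| f | b = 2 points | b = 5 points |
|---|---|---|
| 0.5 | 5.7% | 9.8% |
| 1.0 | 8.0% | 26% |

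Both *b* and *f* are assumptions. The row f = 1.0 is the extreme in which every patient is assessed after the break by someone who knows the arm.

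**The case against.** The best defence is that harm needs a chain of events: a grade 4 event attributed to RAI or prednisolone, a decision to unblind (which is permitted, not required), disclosure to someone who knows the letters, and a grader among those people. The article documents none of the later links. It separates the key holder, the administering investigator and the other investigators, and only the second is said to receive letters. It also describes complications of RAI as rarely serious or life-threatening. Pack labelling and code-break logistics are often left to the full protocol, and the text could, less naturally, be read as assigning A or B afresh for each patient.

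Much of this stands, and it limits the size of the point. It does not remove it. The article states a mechanism and does not merely omit one, and its wording about the identity of A and B points to a single key. A per-patient assignment would need a patient-by-patient key, which is not described.

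Four stronger readings are tempting, and the document does not support them.
- **Bias in patient-reported outcomes.** Nothing says that patients know their letter or would hear of another patient's code break.
- **Steroid effects giving the letter away.** Treatment is one pre-dose plus three daily doses. The article expects few side effects, and dyspepsia and abdominal pain are listed under both RAI and glucocorticoids.
- **Predictable blocks and biased enrolment.** This needs an enroller who tracks letters within strata and guesses the block size. Before the key is known, predicting a letter also gives little reason to select patients.
- **Releasing the key at the end of data collection instead of database lock.** Lock and analyst blinding are commonly set in other documents.

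**Conclusion.** The point holds in a limited form. As described, the scheme cannot unblind one patient to someone who knows that patient's letter without also disclosing what A and B mean. That conflicts with keeping the key from the other investigators until data collection ends. Because the endpoint is graded and attributed clinically, and nothing says the grader is kept from the letters, assessments after a break could be biased.

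The size is unknown. The 4% to 87% range rests on assumed grade 4 rates of 0.01% to 0.5% and counts eligible events. A reader might take it as the risk of losing the blind, but the document gives neither an event rate nor a probability of unblinding after an event. The type I error figures likewise depend on an assumed grading shift. Nor does a break automatically decode all 400 patients to everyone: it decodes those whose letters are known to the people who learn the key.

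The conclusion assumes the natural reading, one A/B key for the trial. This is a cheap improvement to make before recruitment starts, and it does not show that the blind will be lost.

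**What to change.** Replace the A and B labels with unique patient-level kit or code numbers, generated from the stratified blocked list and held by the independent investigator. Provide one sealed code-break per patient, so that opening it discloses that patient's treatment and no other. The wording on concealment and on unblinding would then be consistent.

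The cost is individual pack labelling and one envelope per patient. The tablets are being made specially for this trial and the article states that recruitment has not begun, so the change can still be made. The sample size and analysis are unaffected. When unblinding is clinically warranted stays as the protocol states it.
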